## ***Implementation***

The project will be administered from the Dept of Psychology, University of Oslo, which has the infrastructure to carry out such a study. Data will however be collected, stored and analyzed at Oslo University Hospital through Videoc which is an established and secure system for data collection, storing and management approved by the hospital. The trial will be run at the hospital in the Department of Breast and Endocrine surgery, which is a department with extensive experience in running clinical trials. Two study nurses will be employed to work in the out-patient department and on the ward with patient recruitment and biomarker assessments. A research assistant will be responsible for practical aspects of the trial as well as administering the follow-up data collection which we will attempt to align with the regular medical follow-ups following surgery to ensure a high response rate. Trained therapists and the PhD-student will be responsible for the pre-surgery hypnosis intervention. They will go through didactic and practical training, and complete supervised practice as part of their training. The hypnosis script is already translated and has been pilot tested in a small sample of breast cancer patients ([name] et al *in progress*). The iACT has been developed under the leadership of the co-PI of the study ([name]), with input from our national and international partners ([name] & [name]), and user representatives. The user representatives will further be invited to participate in a focus group upon the completion of the post-operative intervention to discuss their experiences of the intervention and share any advice for modifications or changes to the interventions or procedures.

In order to disseminate the results to patients, clinicians, policy makers and the public, we are planning to co-host a seminar with the Norwegian Cancer Society for stakeholders and

collaborators to present results from the trial. The Cancer Society will also communicate the research findings through their channels, which are well organized and far reaching.

## **Participants**

### ***Number and source of participants***

The study will recruit and randomize 200 participants amongst patients from the Department of Breast and Endocrine surgery at Oslo University hospital (see sample size calculations for justification).

### ***Recruitment***

Eligible patients will be informed about the study by phone and on their first outpatient appointment at the clinic. A study nurse will be responsible for informing and recruiting patients to the trial.

### ***Inclusion criteria***

Patients must fulfill the following criteria to be eligible for inclusion in the study:

- Women diagnosed with breast cancer and scheduled for surgery
- Be able to provide informed consent
- Over the age of 18

### ***Exclusion Criteria***

- Insufficient Norwegian speaking or writing skills to participate in the interventions and fill out questionnaires
- Over the age of 80
- cognitive and psychiatric impairment or
- other serious malignancies

## **Randomization**

The randomization procedure will be administered through the program Viedoc that uses an automated and valid randomization procedure. We intend to use a stratified randomization method in order to balance the influence of covariates. The main covariates of interest here is type of surgery (mastectomy vs breast-conserving surgery) and whether the newly diagnosed breast cancer is a relapse or not. Stratified randomization is achieved by generating a separate block for each combination of covariates, and subjects are assigned to the appropriate block of covariates. After all subjects have been identified and assigned into blocks, simple randomization is performed within each block to assign subjects to one of the groups. Furthermore, a SMART randomization procedure will be applied, where the participants are randomized twice – pre-operative (hypnosis vs a one-session mindfulness), and post-operative (iACT vs treatment as usual).

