## **Interventions**

### *Pre-operative hypnosis*

The pre-operative intervention involves a brief hypnosis intervention that was previously found effective in reducing acute post-surgical pain and fatigue after breast cancer surgery (41). The hypnosis intervention will replicate a previous study of a 15-minute hypnosis intervention (41), and will be provided in a 15-minute session within 1 hour before surgery. The scripted session includes a relaxation-based induction, suggestions for pleasant visual imagery, suggestions to experience relaxation and peace, and specific symptom-focused suggestions. The intervention will be further adapted and modified to the specific context of this study. Trained therapists will hold the session. Patients will be instructed to use hypnosis

on their own following the intervention session. Based on data from the pilot trial, the Norwegian translation and administration of the hypnosis protocol lasts for 20 minutes.

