#### *Post-surgical intervention*

After surgery, participants will be randomized again to either a post-surgical intervention or to treatment as usual. The post-surgical intervention is comprised of a web-based ACT intervention with the cognitive activation model of stress as theoretical vantage points. The intervention consists of videos in combination with a work booklet targeting three main processes derived from the ACT hexaflex model (57), and delivered in two stages. In the initial stage, the intervention has several videos that is built to involve the patient in a broadening of their perspective of what can constitute maintaining and debilitating factors when experiencing persistent pain and/or fatigue. These initial videos involve a biopsychosocial explanation of pain and fatigue, alongside an introduction to mindfulness, values-based living, and stress reduction through cognitive behavioral techniques.

The next stage of the intervention involves the use of a hand-out booklet that serves as an addition to numerous videos presented to the participants. The videos are sorted in three categories aimed to communicate the six processes in a commonsensical, patient friendly way. The three categories are referred to as the tri-flex in the Focused ACT model (58), and consists of Aware (present-moment awareness and self-as-context), Open (Accept and defusion) and Engaged (values and committed action).

Within the booklet there are written tasks corresponding to different videos and scenarios shown in the online intervention to approximate previous trials showing efficacy on chronic pain from a similar intervention (59).

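### The allocation rule waits for a complete patient list that cannot exist before surgery, and simple randomisation within strata does not give the covariate balance the protocol claims

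*Protocol*

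**What the plan says.** The Randomization section of the protocol gives the allocation to Viedoc, which it describes as automated and valid without saying what method it applies. The section states its purpose: "We intend to use a stratified randomization method in order to balance the influence of covariates". The covariates are "type of surgery (mastectomy vs breast-conserving surgery) and whether the newly diagnosed breast cancer is a relapse or not", which makes four combinations. The method is described as "generating a separate block for each combination of covariates", so a block in this text is a stratum and not a permuted block. The rule then follows: "After all subjects have been identified and assigned into blocks, simple randomization is performed within each block". No block size, minimisation or other restriction appears anywhere in the protocol.

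Three other sections fix the order of events for each patient:

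- Recruitment: "Eligible patients will be informed about the study by phone and on their first outpatient appointment at the clinic".
- Pre-operative hypnosis: the session "will be provided in a 15-minute session within 1 hour before surgery".
- Post-surgical intervention: "After surgery, participants will be randomized again to either a post-surgical intervention or to treatment as usual".

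The Randomization section mentions the second randomisation in one sentence and does not say whether it is stratified.

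**The concern.** The rule conflicts with the conduct of the trial and with its own purpose.

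On conduct, a patient's pre-operative arm must be known before her own operation. A rule that starts only when the whole sample has been listed and sorted cannot be applied to patients who arrive, are treated and are operated on one after another.

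On purpose, stratifying balances a covariate only if the allocation inside each stratum is restricted, for example by permuted blocks. Independent draws inside a stratum restrict nothing.

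What is at stake is avoidable chance imbalance in arm sizes and in two factors the investigators themselves consider important, together with a written procedure that staff cannot follow. Bias is not at stake.

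**Working it through.** **1. Timing.** The stated rule puts allocation after all 200 patients are identified. The other sections require the first allocation before each patient's own surgery and the second after it. Both can hold only if the last patient is identified before the first is operated on, and nothing in the protocol plans for that.

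**2. The protocol's own sample size, as background.** Inputs from Sample size and power: difference 1 NRS point, SD 2.4, two-sided alpha 0.05, power 0.80.

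- Normal approximation: n = 2 × (1.960 + 0.842)² × 2.4² / 1² = 90.4, so 91 per group.
- t-test: 91.4, so 92 per group. The stated 92 reproduces. The plan is to include 100 per group.

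**3. Why the strata add nothing under independent draws.** If stratum s holds n_s patients and each is assigned 1:1 independently, the number in arm A in that stratum is Binomial(n_s, 0.5). The sum over strata is Binomial(200, 0.5), and patients' assignments are independent of their covariates. Unstratified simple randomisation has exactly this distribution.

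**4. Arm sizes, X ~ Binomial(200, 0.5).**

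- P(110:90 or worse) = 2 × P(X ≤ 90) = 0.179.
- P(one arm below 92, before attrition) = 2 × P(X ≤ 91) = 0.229.

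**5. Covariate balance.** The protocol gives no stratum shares. The assumed ranges are mastectomy 30–50% and relapse 5–10%. With arms of about 100, the SD of the between-arm difference in a share p is √[p(1−p)(1/100 + 1/100)]:

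- p = 0.30: √(0.21 × 0.02) = 6.5 points.
- p = 0.50: √(0.25 × 0.02) = 7.1 points.

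A simulation of 100,000 trials of 200 patients over the four strata agrees:

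| | Simple within strata | Simple, no strata | Permuted blocks of 4 within strata |
|---|---|---|---|
| SD of mastectomy-share difference (points) | 6.5–7.1 | 6.5–7.1 | 0.9–1.0 |
| P(difference of 10 points or more) | 12–16% | 12–16% | about 0% |
| SD of relapse-share difference (points) | 3.1–4.3 | 3.1–4.3 | 1.2 |
| 95th percentile of arm-size difference | 28 | 28 | 4 |

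The first two columns agree to within simulation error. Block size 4 is only an illustration.

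**6. Effect on power.** t-test, 1 point, SD 2.4, no attrition:

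- 100/100: 83.4%.
- 110/90: 83.1%.
- 114/86 (a difference of 28, the 95th percentile): 82.7%.

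The loss is 0.7 points. An arm below 92 costs little because the other arm is correspondingly larger.

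**The case against.** **The sentence may be a generic description of stratified randomisation of a complete list.** If simple randomisation there means splitting each completed stratum exactly in half, balance would follow. That is a fair reading, and it is why the balance criticism is conditional on independent assignment. It does not rescue the rule, because an exact split needs the finished list, which the timing rules out.

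**Viedoc may already use a sound restricted method.** It may; the protocol does not say. If so, the text misdescribes the method and still needs correcting.

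**The consequence is small.** This stands. Simple randomisation is valid and unbiased, the power cost is under one point, and adjusting the analysis for the two factors, which may be planned in a statistical analysis plan not seen here, would deal with most chance imbalance.

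A reader might infer two further things that the protocol does not support:

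- *That the second randomisation is unstratified, so the four treatment cells are left to drift.* The protocol is silent on this, and silence on a detail that may be specified elsewhere is not an error.
- *That the scheme cannot be programmed in Viedoc.* Only the wait-for-everyone clause is unworkable. Independent draws can be run sequentially in any system, and the protocol says nothing about Viedoc's options.

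**Conclusion.** The point holds as a fault in a stated rule. The timing clause contradicts the protocol's account of recruitment, the pre-operative session and re-randomisation, and this is so on any reading. Read as independent 1:1 assignment, the method also fails its stated aim of balancing surgery type and relapse. Arm-size figures (18% for 110:90 or worse, 23% for an arm below 92) follow from N = 200 and equal allocation alone. The 12–16% for a mastectomy gap of 10 points or more also rests on an assumed mastectomy share of 30–50%.

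Severity is moderate. It would be wrong to conclude that the trial would be biased or materially underpowered because of this rule. Whether 200 patients split over four cells is enough is a separate question, to which chance imbalance adds little.

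**What to change.** Replace the sentence with a statement that each patient is randomised individually at entry through Viedoc, by a concealed restricted method: either permuted blocks of randomly varying size within the four surgery-type by relapse strata, or minimisation on those two factors. Keep the word block for permuted blocks and use stratum for a covariate combination.

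Optionally, state how the second randomisation is done and stratify it by pre-operative assignment, so that the four cells stay near equal.

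The cost is a few sentences and a check that the Viedoc set-up matches them. The change controls imbalance only for patients allocated after it takes effect, so it should be made before the first allocation. If allocation has already begun, the protocol should describe the method actually used.

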## **Interventions**

### *Pre-operative hypnosis*

The pre-operative intervention involves a brief hypnosis intervention that was previously found effective in reducing acute post-surgical pain and fatigue after breast cancer surgery (41). The hypnosis intervention will replicate a previous study of a 15-minute hypnosis intervention (41), and will be provided in a 15-minute session within 1 hour before surgery. The scripted session includes a relaxation-based induction, suggestions for pleasant visual imagery, suggestions to experience relaxation and peace, and specific symptom-focused suggestions. The intervention will be further adapted and modified to the specific context of this study. Trained therapists will hold the session. Patients will be instructed to use hypnosis

on their own following the intervention session. Based on data from the pilot trial, the Norwegian translation and administration of the hypnosis protocol lasts for 20 minutes.

#### *Active control condition*

Patients randomized to the control group will receive a mindfulness based app before surgery. Mindfulness will be delivered via Headspace, a commercially available application which runs on all major smartphones, tablets and web browsers. The Headspace meditation scripts guide users through mindfulness meditations using both audio and visual materials. Internet based mindfulness meditation programs such as Headspace have shown significant effects on chronic pain and fatigue in breast cancer patients (56). However, the referred studies all entail numerous sessions of mindfulness with some degree of therapist involvement. We therefore believe a single session of mindfulness delivered through an app, constitute an active and ethically sound control condition.

#### *Post-surgical intervention*

After surgery, participants will be randomized again to either a post-surgical intervention or to treatment as usual. The post-surgical intervention is comprised of a web-based ACT intervention with the cognitive activation model of stress as theoretical vantage points. The intervention consists of videos in combination with a work booklet targeting three main processes derived from the ACT hexaflex model (57), and delivered in two stages. In the initial stage, the intervention has several videos that is built to involve the patient in a broadening of their perspective of what can constitute maintaining and debilitating factors when experiencing persistent pain and/or fatigue. These initial videos involve a biopsychosocial explanation of pain and fatigue, alongside an introduction to mindfulness, values-based living, and stress reduction through cognitive behavioral techniques.

The next stage of the intervention involves the use of a hand-out booklet that serves as an addition to numerous videos presented to the participants. The videos are sorted in three categories aimed to communicate the six processes in a commonsensical, patient friendly way. The three categories are referred to as the tri-flex in the Focused ACT model (58), and consists of Aware (present-moment awareness and self-as-context), Open (Accept and defusion) and Engaged (values and committed action).

Within the booklet there are written tasks corresponding to different videos and scenarios shown in the online intervention to approximate previous trials showing efficacy on chronic pain from a similar intervention (59).

### ***Comparison of interventions***

*Pre-surgery intervention versus active control:* Hypnosis and mindfulness are commonly regarded as supplements or integrative parts of an ACT intervention (43). They both start by focusing the patient's attention in similar ways, but proceed to utilize that focused state into different means. The pre-operative hypnosis here is used with a specific purpose and intent of lessening pain and promote coping. The pre-operative one-session mindfulness has a specific purpose and intent to focus on one thing like the breath, sounds or the body. Thus, both techniques guide the patients experience and use suggestion, but the end goals are fundamentally different.

### **Drop out and non-compliance**

Participants who no longer wish to participate in the study can inform the research group of their decision by notifying the study nurse, the trial coordinator or the PI. The trial

coordinator will in any case contact participants who drop out by phone, and ask if they are willing to report the reason for withdrawal. If reasons are provided, these will be registered on a dedicated drop out form. Whether they only want to withdraw from the interventions, or if they also want to withdraw from future follow-ups, will also be registered. Finally, it will be registered if the participant gives permission for use of data that has already been collected, or if they want these to be deleted. Participants who drop out of the study will still be included in the intention-to-treat (ITT) analyses, unless they required all their data deleted.

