Unmodifiable risk factors for CPSP involve female gender and younger age (12), as well as preoperative pain conditions and use of opioids (12, 13, 18, 19). However, a preventive intervention could target psychological factors, which are both modifiable, robust and potent predictors of CPSP and fatigue (14, 20). The most frequent tap into anxiety, such as hypervigilance and pain catastrophizing (20-24). Other strong predictors involve depression, stress, and optimism (10, 14, 23).

Despite strong evidence supporting the role of psychological factors in the development of CPSP and fatigue, hardly any studies have investigated psychological and behavioral interventions aimed at preventing these symptoms. CPSP and fatigue *management*, however, has been the aim of several psychological and behavioral interventions. Mindfulness-based cognitive therapy on persistent pain after breast cancer surgery was recently found effective in reducing pain intensity (25), and a study led by a member of our project group found beneficial effects of CBT plus hypnosis to control fatigue in patients undergoing radiotherapy for breast cancer (26). Several studies of similar psychological interventions exist, but with limited effects (27, 28), and with no preventive focus (29-31).

Hypnosis is a non-pharmacotherapeutic technique that holds promise as a harmless and effective pre-operative intervention to alleviate acute post-surgical pain and fatigue (32, 33). Clinical research with at least 20 different surgical populations has indicated that hypnosis can reduce the need for medication, reduce post-surgical symptoms, and enhance recovery (33). Furthermore, meta-analyses (34), narrative reviews (35, 36), and randomized clinical studies (37-40) all support the potential clinical utility of hypnosis with surgical breast cancer patients. A rigorous trial from 2007 demonstrated particularly large effects of a specific 15-minute pre-operative hypnosis on analgesic needs, pain intensity and fatigue after breast cancer surgery (41). However, the results from this trial have not been replicated, and results from hypnosis trials in general lack long-term follow-up.

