## **Methods/Design**

### **Aims and objectives**

The primary aim of the study is to develop and test an easily implementable strategy of preventing persistent pain and fatigue after breast cancer surgery. The intervention strategy involves a pre-operative hypnosis session and a post-operative, internet-based Acceptance and Commitment Therapy (iACT). The hypnosis was previously found effective in alleviating acute post-operative pain and fatigue in breast cancer patients, while ACT may be particularly well suited to cancer populations as it offers a model of healthy adaptation to difficult circumstances. Together they form an intervention strategy with both a preventive and a rehabilitative focus.

We have the following hypotheses:

- 1) Hypnosis is more effective than one-session mindfulness in relieving acute post-surgical pain and fatigue
- 2) Hypnosis alters markers of bodily stress responses and impacts immune reactivity associated with pain and fatigue.
- 3) Hypnosis + iACT results in less post-surgical pain and fatigue and fewer medical prescriptions for pain medication 3 months after surgery compared to one-session mindfulness + TAU

- 4) Hypnosis + iACT is favorable in a cost-utility analysis, and will result in fewer days of sick leave at 1 year follow-up compared to one-session mindfulness + TAU
- 5) Hypnosis + iACT results in less psychological distress and fewer medical prescriptions for psychotropic medications at the 3 and 6-month follow-ups compared to one-session mindfulness + TAU

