## **Outcome Measures**

To assess hypothesis 1, subjective experiences of pain intensity, pain unpleasantness, and fatigue will be assessed using the Numerical Rating Scale (NRS) and Visual Analogue Scales (VAS) after surgery, upon discharge. Both intensity (i.e., amount) and unpleasantness of pain will be assessed to capture its sensory and affective dimensions. Two 100-mm visual analog scales (VASs) will be used to assess fatigue and muscle weakness, in line with previous breast cancer trials of post-surgical fatigue (26, 41).

To assess hypothesis 2, we will measure cortisol in hair as a marker of hypothalamus-pituitary-adrenal (HPA) axis activity, and two measures of inflammation – high sensitive CRP

(hs-CRP) and lipopolysaccharide (LPS) reactivity. We consider hs-CRP an acceptable initial marker of systemic inflammation, whilst LPS will provide more nuanced and detailed results of immunological reactivity.

To assess hypothesis 3, NRS will be used to measure post-surgical pain, and FACIT-F (51) to measure post-surgical fatigue at 3 months follow-up. Registry data on pain-related prescriptions will further be extracted from The Norwegian Prescription Database (NorPD).

To assess hypothesis 4, we will use registry data to estimate the number of days participants in each group have been on sick leave (or other welfare benefits) during the year following surgery.

To assess hypothesis 5, we will measure psychological distress by the Hospital Anxiety and Depression Scale (52), as well as data on psychotropic prescriptions from The Norwegian Prescription Database (NorPD).

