### **Data collection and management**

Self-reported data and biomarker data will be collected pre-surgery (questionnaires, hair and blood), post-surgery upon discharge (brief phone survey), 3-4 weeks after surgery (blood), as well as 3 and 6 months after surgery (only questionnaire data). These time points either align with clinical follow-ups at the outpatient oncology department, or are responded to through an

electronic link in the patients' homes to avoid unnecessary strain on the patient. Patient charts will be used to collect data on surgical procedures and potential complications during/after surgery. This will include information about the duration of the surgery, tumor-related variables, severity of acute post-surgical pain, and other relevant intra-operative variables. Registry data on employment and benefit take-up and medical prescriptions will be obtained from FD-Trygd and the Norwegian Prescription Database (NorPD), respectively. To be able to assess for the effects of the interventions, data from NorPD and FD-Trygd will be obtained from inclusion in the trial until one year follow-up. The NorPD contains data about dispensed drugs in Norway, while FD-Trygd contains social security micro data for research. These data will be obtained retrospectively. The post-operative booklet that the patients receive as part of the iACT will also be collected at 6 months follow-up to assess if the patients used it as intended.

----- INSERT FIGURE 1-----

Survey data will be collected electronically by the use of laptops/smartphones. We will also utilize data from patients' medical records regarding surgical procedures and medical variables, as well as registry data, which will be linked to the survey data. Data from medical records as well as test results from blood samples will be entered directly into Viedoc by our study nurse. All data will be stored on a secure server at the hospital. The hospital already have a system in place for secure collection and storing of sensitive data which will be used.

A detailed plan for data management and sharing will be developed in collaboration with both Oslo University and the University of Oslo that shares the responsibility for data management in this study.

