**Ethics approval and consent to participate**

The study will comply with good clinical practice, including the most recent version of the declaration of Helsinki, as well as all relevant rules and regulations of Norway. The study will be submitted to the Regional ethical committee and the Data Protection Officer at Oslo University Hospital as well as the Data Protection Officer at Oslo University for approval. All participants have signed a statement on consent to participate. The right to withdraw from the study at any time without any explanation, and without any consequences for the further treatment at the clinic, will be emphasized.

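### The protocol defines no systematic, arm-neutral record of unwanted effects of hypnosis, the mindfulness app or iACT

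*Protocol*

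**What the plan says.** **Collection.** Protocol, Outcome Measures and Data collection and management, cover pain, fatigue, distress, biomarkers, registry prescriptions and sick leave, with further questionnaires described under their own subheadings. On clinical events, "Patient charts will be used to collect data on surgical procedures and potential complications during/after surgery". On distress, "we will measure psychological distress by the Hospital Anxiety and Depression Scale (52), as well as data on psychotropic prescriptions"; the matching hypothesis in Aims and objectives concerns "less psychological distress and fewer medical prescriptions for psychotropic medications at the 3 and 6-month follow-ups". The contact at discharge is a short telephone survey, and the outcomes named for it are pain intensity, pain unpleasantness, fatigue and muscle weakness. No item, form, time point or analysis for unwanted effects of an intervention appears.

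**Withdrawal.** Under Drop out and non-compliance, the "coordinator will in any case contact participants who drop out by phone" and is to "ask if they are willing to report the reason for withdrawal. If reasons are provided, these will be registered on a dedicated drop out form". The same section distinguishes stopping the interventions from leaving follow-up as well, and lets a participant have her data deleted.

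**Context.** The Background states: "Hypnosis is a non-pharmacotherapeutic technique that holds promise as a harmless and effective pre-operative intervention". Under Ethics approval and consent to participate: "The study will comply with good clinical practice". The primary aim is a strategy that is easy to put into practice.

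**The concern.** A woman who is distressed by the hypnosis session, the app or the iACT videos, and who carries on, has no planned opportunity to say so in a form that links the experience to what she received. The trial could then report benefit with no count and no denominator for unwanted effects, and that silence could be read as evidence of safety. This matters because the aim is wider use. It is also not something an analysis plan can repair, since an analysis plan cannot recover data that were never collected.

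**Working it through.** **1. What each planned source can show**

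| Source (Protocol section) | Who is covered | Brief reaction to the pre-operative session? | Attributes an event to an intervention? |
|---|---|---|---|
| Discharge survey: pain, fatigue, muscle weakness (Outcome Measures) | All | Only if it shows as one of these symptoms | No |
| Chart complications (Data collection and management) | All | Not as such; the scope is surgical | No |
| HADS and psychotropic prescriptions, compared at 3 and 6 months (Aims and objectives; Outcome Measures) | All | No; months later | No |
| Pain and fatigue at 3 and 6 months; pain prescriptions | All | No | No; radiotherapy or chemotherapy may be under way (Sample size and power) |
| Withdrawal reason (Drop out and non-compliance) | Women who withdraw and agree to answer | Possibly | Possibly, in her own words |
| Focus group (Implementation) | User representatives | No | Not systematic |

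Hypnosis is given within an hour before surgery (Pre-operative hypnosis), so the discharge survey is the only planned contact close enough to catch a passing reaction.

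**2. Opportunity for staff to observe**

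A therapist holds the hypnosis session, and the principal investigator and co-investigator supervise the therapists (Compliance). The pre-operative control is an app. iACT is videos and a booklet, followed through usage logs and booklet collection. Any incidental staff observation would therefore arise more easily for hypnosis.

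**3. The plan's own figure**

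The point rests on no stated figure, but 92 is used below as a responder count, so it was checked. Inputs from Sample size and power: difference 1, SD 2.4, two-sided alpha 0.05, power 0.80.

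- Normal approximation: n = 2 × (1.960 + 0.842)² × 2.4² / 1² = 90.4, so 91 per group.
- The t-based calculation gives 91.4, so 92, as stated.

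**4. What asking everyone would give**

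With zero events in n answers, the exact upper bound is p = 1 − a^(1/n), with a = 0.05 one-sided or 0.025 for a two-sided 95% interval.

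| n answering | One-sided 95% | Two-sided 95% |
|---|---|---|
| 100 (one pre-operative group) | 2.95% | 3.62% |
| 92 | 3.20% | 3.93% |
| 50 (one of four treatment sequences, if 200 split equally) | 5.82% | 7.11% |

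The chance of at least one event among 100 is 1 − (1 − p)^100: 63% at a true rate of 1%, 87% at 2%, and 99% at 5%.

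**5. What the withdrawal reason alone would give**

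Share of affected women recorded = P(withdraws, given an unwanted effect) × P(gives the reason). The protocol states neither. Assumed ranges are 8% to 50% for the first and 50% to 100% for the second.

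- Lowest: 0.08 × 0.50 = 4%. Highest: 0.50 × 1.00 = 50%.
- A zero count in a group of 100 bounds the recorded rate at 2.95%. The true rate is then bounded at 2.95% / 0.50 = 5.9% in the best case and 2.95% / 0.04 = 74% in the worst.

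Because the share is unknown, a zero on the form bounds nothing useful.

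**The case against.** The strongest reply is that harm-relevant data are already planned for everyone. Distress is a compared outcome, and pain, fatigue, prescriptions and surgical complications do not depend on withdrawal, so lasting worsening on iACT should show in the randomised comparison. This stands, and it narrows the gap to passing reactions and to attribution. The interventions are also brief or self-directed, which argues for a light remedy.

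Four stronger readings are tempting, and the protocol does not support them.

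- **Unwanted effects are collected only from drop-outs.** The withdrawal form is not presented as harms collection. The outcomes above cover all participants, and the form also reaches women who stop an intervention but stay in follow-up.
- **The trial rests on hypnosis being harmless.** The wording is a hedged background remark, and none of the five hypotheses concerns harm.
- **Harms data will be biased against hypnosis.** The withdrawal call is the same in every arm, and no route is described for therapists to report what they see. Unevenness is possible because only hypnosis has a live therapist; it is an inference about direction and cannot be quantified.
- **The planned allowance caps how many women could give a reason.** The margin of 100 − 92 = 8 per group is a power allowance for pain. On the fatigue figure it is 100 − 87 = 13. Actual withdrawals could exceed either.

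It can also be said that the withdrawal text is not itself wrong. That is so. The defect is in the data collection, and the withdrawal text matters because it is the only direct route.

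**Conclusion.** The point holds in this form: no systematic, arm-neutral collection of unwanted effects is defined, and a voluntary withdrawal reason is the only direct record. A trial run as written could not support the suggestion that hypnosis is harmless. Asking everyone would turn zero events in 100 into a one-sided upper bound of about 3.0% (two-sided about 3.6%; one-sided about 3.2% with 92 responders), whereas the withdrawal form yields no usable bound.

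This rests on three assumptions: that the 200 women split equally between the pre-operative groups; that all those counted answer; and that the figure referred to in Data collection and management, which is not shown in the text at hand, adds no such item. The primary efficacy comparison is unaffected. The change is worth making because the information cannot be reliably recovered afterwards.

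**What to change.** In Data collection and management, add one item to the discharge telephone survey and to the 3- and 6-month questionnaires, worded identically for all participants. For example: any unwanted or distressing experience since the last contact, how severe it was, and whether she links it to any study activity. Asking about any experience first keeps the item meaningful for women on treatment as usual, who have no post-operative programme to comment on.

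Record the answers in Viedoc. Have them reviewed without knowledge of allocation where feasible, since the principal investigator and co-investigator supervise the hypnosis and the co-investigator led the development of iACT. Report counts with denominators by randomised group at each stage, and list therapist-observed events separately so that they do not enter the between-arm comparison.

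Cost: a minor amendment, one item at three existing contacts, one Viedoc form, and slightly more respondent and review time. No extra staff or visits are needed.
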